## Introduction

Suicide is a leading threat to the well-being of communities globally, and particularly in India which reports the highest number of suicide deaths in the world.
^
1
^ Although Indians make up 18% of the world’s population, India accounts for 26.6% of suicides globally.
^
2
^ Since 2017, suicide rates in India have increased steadily with suicide ranking as the first and second leading cause of death among young women and men aged 18-39 respectively.
^
3,
4
^ Data from the National Crime Records Bureau (NCRB) indicates an upward trajectory, with a national suicide rate of 12.4 per 100,000 individuals in 2022 up from 12 in 2021, marking the highest rate in NCRB history.
^
4
^ This is despite a recognized under-reporting of suicides in India by as much as 30-100%.
^
3,
5
^

Chhattisgarh, a central Indian state, has a suicide rate of 28.2 per 100,000 (2022), the fourth highest among states in India and more than double the national suicide rate of 12.4 per 100,000.
^
4
^ The Chhattisgarh District Mental Health Program (DMHP) was designed to offer telephonic and in-person follow-up counselling for individuals who have attempted suicide; however, most DMHP clinics are unable to implement the intended program due to a dearth of specialized providers, such as psychiatrists, psychologists or counsellors trained to respond to suicide. Consequently, in many districts, there is no follow-up by a professional after a suicide attempt, despite prior research demonstrating that a previous suicide attempt is one of the strongest predictors of future attempts.
^
6,
7
^

Although the State Government of Chhattisgarh is drafting a State Suicide Prevention Strategy (not yet published); the lack of human resources is a significant constraint in the state which necessitates the mobilization of public health resources to implement suicide response and prevention measures. Contact and Safety Planning (CASP) is an adaptation of brief intervention and contact (BIC) and safety planning interventions, methods which have been effective in reducing suicidal behavior among high-risk individuals worldwide.
^
7–
10
^ CASP was developed and adapted from evidence-based safety interventions for the Indian context by SNEHA, Chennai and showed to be effective, feasible and acceptable when delivered among a refugee population in Tamil Nadu.
^
8
^ BIC has been effective in reducing repeat suicides in a 5-country study
^
11,
12

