## Protocol

### Aims

The primary aims of this study are to assess the feasibility, acceptability, reach, adoption and implementation (including cost) of delivering the CASP intervention within the public health system in Chhattisgarh.

The secondary aim is to assess:
•Difference in rate of suicide re-attempt at 6 and 12 month follow up between intervention and control groups,•Preliminary impact on suicidal behaviour and symptoms of depression at 6 and 12 month follow up within the intervention group only.

For the purposes of this study, suicidal behaviour is defined as inclusive of suicidal intention, ideation, planning and fatal or non-fatal suicide attempt.

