### Study design

The CASP intervention will be tested in the form of a 1:1 non-randomized, controlled pilot study. The pilot study will consist of two arms, comparing the CASP intervention in the two districts of Balod and Rajnandgaon against Enhanced Usual Care in the two districts of Mungeli and Balodabazar.

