month follow up. The Modified C- SSRS Screener is a semi-structured tool which measures the risk of suicide by inquiring about suicidal behaviour in the person’s lifetime (baseline) and since the last contact point (follow up). The screener consists of 6 questions and can be completed in a few minutes. For the purposes of this study, a lifetime measure was added to the screener to collect data on previous history of suicide ideation and behaviour at baseline. Specifically, the tool explores:
1.The presence of thoughts about suicide (suicidal ideation),2.Actions taken by the individual, in relation to preparing for suicide,3.Instances when the person has either attempted suicide or initiated a suicide attempt that was interrupted by another person or halted voluntarily, and the timing of this (lifetime, since last contact).

The C-SSRS has been translated in over 60 countries (including Hindi, and in India) and takes approximately 5 minutes to complete when administered as a clinical interview. The scale can be used by non-specialists across a range of settings, including healthcare settings.
2.Symptoms of depression

The Hindi Patient Health Questionnaire (PHQ-9)
^
25
^ assessment can be used as a screening tool as well as measures of symptom severity for depression. The nine-item PHQ-9 uses a 4-
point Likert-scale with items ranging from 0 (not at all) to 3 (nearly every day). The PHQ-9 has been validated, widely used, and found to be suitable for use in India.
^
26
^

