### Data collection

Baseline demographic data—including age, gender, education, marital status, employment status, caste/tribal background, income, and contact details—will be collected by Community Health Officers (CHOs) from consenting participants. Study records will include the following: (1) record books maintained by nurses at health facilities, documenting the date, age, gender, method of attempt, verbal consent status, and, if applicable, reasons for refusal; and (2) CHO records detailing the dates and locations of participant visits to monitor adherence to the CASP intervention schedule (at 1, 2, 4, 7, and 11 weeks post-attempt).

For outcome assessments, the Columbia-Suicide Severity Rating Scale (C-SSRS) and the Patient Health Questionnaire-9 (PHQ-9) will be administered to participants in the intervention group at baseline and during follow-ups at 6 and 12 months. Within the control arm, a brief follow up survey will be administered that captures suicide re-attempt at 6 and 12 month follow up points. Data collection will be conducted by trained data collectors, who are local Master’s graduates in mental health or related fields with prior experience in the health system.

To support the cost analysis and economic evaluation, a brief cost survey (Modified TiC-P) and the EuroQol-5D-5L will be administered to a random sample of 50 participants in both the intervention and control groups at baseline and at the 6-month follow-up. Data collection will be conducted using paper-and-pencil assessments or self-administered forms, based on participant preference.

Qualitative follow-up data will be collected through in-depth and semi-structured interviews, lasting approximately one hour each. These interviews will be conducted by research team members and audio recorded with prior informed consent for transcription purposes. Acceptability interviews with participants will include a random sample selected independently of intervention completion status, ensuring the inclusion of individuals who may have dropped out of the study. See
Figure 1 for research and data collection procedures.

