## Ethics and consent

Ethical approval has been obtained from Indian Law Society’s Institutional review board (ILS/173B/2022) dated 26 September 2022, the University of Utrecht Ethical Review Board, Netherlands (#23-0003) dated 1 October 2022 and the Clinical Trials Registry India (CTRI) (CTRI/2022/12/048087) for this study. All procedures will be done in adherence to guidelines outlined in the Declaration of Helsinki, including obtaining written informed consent from participants, ensuring confidentiality, and protecting participants’ rights, privacy and well-being. Written consent will be collected by Community Health Officers in the intervention districts and by data collectors in the control districts. Authorship of any publications which emerge from this project will be agreed upon by all authors based on individual contribution to the manuscript, project implementation, concept, steering, and evaluation.

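### Lifetime attempt history (C-SSRS) and PHQ-9 are taken only in the CASP arm, so the non-randomised re-attempt comparison cannot be checked or adjusted for earlier attempts or baseline depression

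*Protocol article*

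**What the plan says.** Study design describes a "1:1 non-randomized, controlled pilot study" with two whole districts per arm. Among the secondary aims is the "Difference in rate of suicide re-attempt at 6 and 12 month follow up between intervention and control groups"; the same list confines the assessment of suicidal behaviour and depression symptoms to the intervention group.

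Data collection follows that split. The C-SSRS and PHQ-9 "will be administered to participants in the intervention group at baseline and during follow-ups at 6 and 12 months". The next sentence reads: "Within the control arm, a brief follow up survey will be administered that captures suicide re-attempt at 6 and 12 month follow up points".

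Under Outcomes, the account of the C-SSRS explains that "a lifetime measure was added to the screener to collect data on previous history of suicide ideation and behaviour at baseline". No other source of attempt history is described for either arm. The nurses' record books hold date, age, gender, method of attempt and consent status. The cost sub-sample (TiC-P and EQ-5D-5L, 50 per arm) is measured at baseline in both arms, but neither instrument records attempt history or PHQ-9.

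Ethics and consent states that written consent is taken by CHOs in the intervention districts and "by data collectors in the control districts".

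**The concern.** Without randomisation, the case for reading a difference in re-attempt as an effect of CASP depends on showing that the arms had similar prognosis at entry, or on adjusting for what differed. The protocol's own figures show that the district populations are not alike. Setting gives Scheduled Tribe shares of 26% and 31% in the intervention districts against 12.8% and 10.37% in the control districts, and Scheduled Caste shares of 10% and 8% against 23.37% and 27.76%. The control districts also have an active mental health programme and monthly awareness camps that the intervention districts lack, which could alter who presents. The Discussion adds that records of attempts in control districts are not systematic, so case capture may differ as well.

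A different mix of first-time and repeat attempters, or of depression severity, is therefore plausible. The protocol fixes measurement of both in one arm only. This is not a matter that an analysis plan can settle later, because no model can adjust for a covariate that was not recorded in half the sample. At stake is the interpretation of the preliminary effectiveness estimate, not the primary implementation outcomes.

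**Working it through.** The plan gives no figure for this point, so there is none to reproduce. The check has two parts.

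**1. What is available in each arm at baseline**

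| Item | CASP arm | Control arm |
|---|---|---|
| Attempts before the index attempt (C-SSRS lifetime items) | yes | no source described |
| PHQ-9 | yes | no source described |
| Age, gender, method of attempt (nurse records) | yes | possibly; use of the books there is not spelled out |
| Demographic survey | yes, by CHOs | unclear; Outcomes does not limit it to one arm |
| EQ-5D-5L, including an anxiety/depression dimension | 50 participants | 50 participants |

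The Outcomes section describes the C-SSRS without naming an arm, but Data collection is explicit and Aims agrees with it.

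**2. How far an unseen imbalance could move the result**

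Inputs from the protocol: control re-attempt risk 10% at 12 months, 250 per arm, 20% loss (Sample size). Evaluable per arm: 250 × 0.80 = 200.

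Inputs assumed, not in the documents: 30% of control participants with an earlier attempt; risk ratio R of 2 to 3 for re-attempt in that group; a difference of 10 to 20 points between arms in the share with an earlier attempt; no intervention effect.

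Risk without an earlier attempt: r0 = 0.10 / (0.7 + 0.3R). Risk with one: r1 = R × r0. Spurious difference = (r1 − r0) × difference in share.

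- R = 2: r0 = 0.10/1.3 = 7.7%, r1 = 15.4%, gap 7.7 points. Times 0.10 to 0.20: **0.77 to 1.54 points**.
- R = 3: r0 = 0.10/1.6 = 6.25%, r1 = 18.75%, gap 12.5 points. Times 0.10 to 0.20: **1.25 to 2.5 points**.

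Standard error of the crude difference at 10% in both arms: √(2 × 0.10 × 0.90 / 200) = √0.0009 = 3.0 points, so a 95% interval is about ±5.9 points (1.96 × 3.0).

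Wider assumptions (R from 1.5 to 4, shares between 20% and 40%) give about 0.4 points (R = 1.5, 30% against 20%: 0.10 × 1.10/1.15 = 9.57%) to about 3.8 points (R = 4, 20% against 40%: 0.10 × 2.2/1.6 = 13.75%). As a yardstick only, since the plan uses a Bayesian test, a two-sided 5% test with 200 per arm would reject in about 5% to 21% of trials over that range.

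**The case against.** **Is the predictor the protocol's own?** The Introduction says that "a previous suicide attempt is one of the strongest predictors of future attempts", and a reader might infer that the protocol itself ranks earlier attempts as a leading predictor among its participants. It does not. The sentence justifies following up people who have just attempted suicide, and every participant in both arms has that index attempt. That attempts before the index one also predict re-attempt in this population is a reasonable working assumption, not a statement of the document.

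**Are control demographics missing?** A reader might infer this because only CHOs are named as collecting them. The text does not support it. The demographic survey is not limited to one arm, the article is written largely from the intervention side, and the flowchart is not shown.

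**Is the information lost for good?** Not entirely. Earlier attempts can be asked about at the 6- or 12-month survey. What cannot be recovered that way is baseline PHQ-9, and history for those who died or were lost.

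**Is the CASP-arm history wasted?** No. It serves the stated within-arm aim.

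**Size and rank.** The shift rests on assumed inputs and stays below one standard error in the central range; only the extreme of the wider range exceeds it. Re-attempt is a secondary outcome of a pilot, and no progression criterion uses it. This stands, and it limits the weight of the point.

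**Would the fix rescue the inference?** Only in part. With two districts per arm that differ in services, individual covariates cannot remove district-level confounding. Timing also limits it: data collection ends in November 2025, so anyone with a full 12 months of follow-up must be enrolled by about November 2024, and few enrolments may remain.

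What survives is narrower: two individual-level markers relevant to prognosis are recorded in one arm by stated design, and at least one can be obtained in the other at little cost.

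**Conclusion.** The point holds in a limited form. By explicit choice, the protocol records attempt history and PHQ-9 in the CASP arm only, so the between-district re-attempt difference cannot be checked or adjusted for either. Partial checks on other variables may be possible, so the comparison is not wholly uncheckable. A plausible imbalance in attempt history would shift the crude difference by about 0.8 to 2.5 points, assuming 30% prevalence, a risk ratio of 2 to 3, a 10 to 20 point imbalance and 10% control risk. That is modest beside a standard error of about 3 points, but it is a bias, and a larger sample would not reduce it. An imbalance in depression severity could add to it or offset it. The change is a worthwhile, inexpensive improvement to a secondary comparison. Nothing here undermines the implementation outcomes or the within-arm analyses.

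**What to change.** In Data collection, state that the control-district data collectors who already take written consent also record the C-SSRS lifetime attempt items and the PHQ-9 for all remaining enrolments. For control participants already enrolled, add a question on attempts before the index attempt to the 6- or 12-month survey, worded so that neither the index attempt nor a later re-attempt is counted.

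In Data analysis, show both arms' baseline side by side. Alongside the planned comparison, report one adjusted for earlier attempts, and for PHQ-9 where it was measured. State plainly that district-level confounding remains.

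Cost: a few minutes per control participant (the article puts the C-SSRS at about 5 minutes; the PHQ-9 has nine items) and an ethics notification. No new staff or visits should be needed, although the article does not give the timing or mode of the control consent contact. There are also drawbacks to report. The control arm receives some added assessment contact. Recalled history is less accurate than baseline history and is collected differently from that in the CASP arm. It will be missing for those who died or were lost.

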**Figure 1. f1:**
[figure not shown]
Flowchart of research procedures.

### Data analysis

*Implementation outcomes*

Descriptive statistics (means, medians and standard deviations) of the reach, adoption and implementation metrics will be calculated. Qualitative thematic analysis
^
27
^ of the in-depth interviews exploring feasibility and acceptability will be carried out using a mix of inductive and deductive approaches. Two coders will independently review transcripts, generate initial codes, and collaboratively develop a comprehensive codebook (initial coding). This will be followed by a pilot coding phase to ensure procedural consistency before independent coding of the remaining transcripts, with discrepancies resolved through consensus or third-rater consultation. Researchers will then interpret and refine final themes. Coding will be done using NVivo 1.4.1.

*Clinical outcomes*
1.Difference in percentage of re-attempted suicide and death by suicide

We will analyze the difference between the intervention and control group in the percentage of participants who, after initial visit in the hospital for a suicide attempt, have re-attempted suicide (including deaths by suicide) at 6 and 12 months of follow-up. For statistical analysis, we will use Bayesian binominal testing as implemented in the open software program JASP.
^
28
^ Bayesian analysis allows us to not only test whether the null hypothesis is true or false, but also to test how likely the alternative hypothesis (that the change in suicide rates between intervention and control) is given the data.
^
29,
30
^
2.Change in depression, suicide risk and TiC-P scores

The mean change in depression and suicidal behavior scores between baseline and 6-
and 12-
months follow-up within the intervention group will be calculated using Bayesian linear mixed models as implemented in JASP. Models will be estimated both with and without a random effect for location, to see if it is needed to control for any clustering effect.
^
31
^
3.Quality of life

Analyses using EQ-5D-5L data will be presented in various ways. A basic subdivision will be made according to the structure of the EQ-5D-5L: 1) Presenting results from the EQ-5D-5L descriptive system as a health profile for each dimension; 2) Presenting results of the EQ VAS (visual analog scale) as a measure of overall self-rated health status, and 3) Presenting results from the EQ-5D-5L index values. The index values, presented in country specific value sets, are a major feature of the EQ-5D-5L instrument, facilitating the calculation of quality-adjusted life years (QALYs) that are used to inform economic evaluations of health care interventions. Mean change in QOL from baseline to end of follow-up will be presented separately in both control and intervention arms. An appropriate Bayesian linear mixed model using logit link and ordinal family will be employed depending on the data.
4.Economic evaluation

The cost analysis will evaluate the CASP program from health system (program implementation costs), patient (e.g., healthcare expenses, quality of life), and societal (e.g., productivity losses) perspectives. Healthcare expenses and productivity losses will be measured using the TiC-P, and quality of life will be assessed with the EQ-5D-5L. Implementation costs will be calculated by the research team based on start-up and recurring costs. Patient costs will be calculated using a bottom-up (micro-costing) approach: each item in the TiC-p will be multiplied by an appropriate unit cost and summed to provide an overall total cost. Given that references’ prices do not exists for India, unit prices will be determined based on previous studies
^
32
^ and international recommendations.
^
33
^ All cost prices will be converted to the 2024 price levels. Using EQ-5D-5L utilities, the area under the curve method will be used to compute quality-adjusted life years (QALYs) by using the utilities at baseline and 6 months follow-up (i.e. linear interpolation).

The economic evaluation will constitute a cost-utility analysis with QALYs as central outcome. To simultaneously evaluate both costs and outcomes, baseline-adjusted seemingly unrelated regression equations (SURE) models will be used. Given that costs are usually non-normally distributed the SURE models will be bootstrapped (2,500 times). To allow for intention to treat analysis, single imputation (based on predictive mean matching) nested in each bootstrap simulation will be used, as recommended by Brand and colleagues.
^
34
^ For each bootstrap simulation, incremental cost-effectiveness ratios (ICERs) will be calculated by dividing the incremental costs by the incremental QALYs, resulting in the costs per QALY gained. Next, ICERs will be plotted on a cost-effectiveness plane and a cost effectiveness acceptability curve (CEAC) will be constructed to determine the probabilities that the new intervention is cost-effective given a range of WTP values for a QALY.
^
35
^ Given the lack of formal WTP thresholds, a WTP ceiling of three times the national annual gross domestic product (GDP) per capita has been recommended.
^
36
^ Sensitivity analyses will be directed towards the main drivers of costs and QALYs.

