### Setting

The Central Indian state of Chhattisgarh, formerly a part of Madhya Pradesh, was granted statehood in 2000 and is the ninth largest state in India (estimated population 25.5 million).
^
15
^
^,^
^
16
^ 75% of the population live in rural areas and the state has the highest tribal population among large states in India with one-third of its population belonging to tribal communities.
^
16,
17
^ Chhattisgarh is divided into 32 districts as of 2021, 28 of which are covered by the Government’s District Mental Health Program (DMHP).
^
18
^ In 2022, Chhattisgarh contributed 4.9% of India’s suicide burden, with a rate of 28.2 per 100,000 people, more than twice the national average (12.0).
^
4
^ According to the National Mental Health Survey (2016), approximately 0.28% of the population in Chhattisgarh is at high risk of suicide, with the highest risk group being 18–29-year-olds.
^
15
^ As per the NCRB, factors which contribute to suicide in Chhattisgarh include financial difficulties among men such as bankruptcy or indebtedness, and marriage related problems among both men and women.
^
4
^ The mental health treatment gap is also high in Chhattisgarh, ranging from 54.5 % (for psychosis) to 80.1% (for common mental disorders).
^
19
^

*Intervention district selection*
^
16
^

Rajnandgaon is home to an estimated 1.8 million people, with 82.27% residing in rural areas. The population includes 26% Scheduled Tribe (ST) and 10% Scheduled Caste (SC) communities and shows a 52% work participation rate. As a larger district, Rajnandgaon consists of 6.02% of the state’s population. It comprises 9 blocks with 1 district hospital, 1 medical college, 10 community health centres, and 47 primary health centres.

Balod district is home to approximately 0.8 million people, with 88% living in rural areas. 31% of the population belong to ST communities, and 8% to SC communities. The district’s work participation rate is 51%, and it is divided into 5 blocks and 704 villages. The healthcare infrastructure includes 1 district hospital, 5 community health centres, and 30 primary health centres.

Both districts lack follow-up care for attempted suicide cases in healthcare facilities, a gap this study aims to address by training health workers placed at multiple levels of the health system in these districts.

*Control district selection*

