Balodabazar and Mungeli are two predominantly rural districts in Chhattisgarh. Balodabazar has a total population of approximately 1.31 million, with 87.25% residing in rural areas. The district’s population includes 23.37% Scheduled Castes (SC) and 12.8% Scheduled Tribes (ST). The district is administratively divided into six blocks and is served by one district hospital, six community health centres (CHCs), and 31 primary health centres (PHCs).

Mungeli has a smaller population of approximately 0.70 million, with an even higher rural proportion (90.67%). Its population comprises 27.76% SC and 10.37% ST. Mungeli consists of three blocks and is served by one district hospital, three CHCs, and 28 PHCs.

Like Balod and Rajnandgaon, Balodabazar and Mungeli are characterized by a predominantly rural, socially disadvantaged population and limited health infrastructure.

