### Control condition: Enhanced Usual Care (EUC)

In Chhattisgarh, usual care under the DMHP includes a telephonic follow-up, where a social worker or a clinical psychologist at the DMHP clinic provides counselling for an individual who has recently attempted suicide, and invites them to visit the DMHP clinic in person to receive continued support. However, some clinics (such as in as our intervention districts) do not have any existing follow up care for suicide due to staff shortages, and so the CASP pathway will serve as the primary follow-up response in these districts. In the control districts, participants will receive Enhanced Usual Care (EUC). EUC will consist of the usual care provided by the District Mental Health Plan (DMHP) in Balodabazar and Mungeli, which have an active DMHP program staffed by a social worker, a nurse as well as a psychiatric nurse, a clinical psychologist and a Medical Officer (MO) (a medical professional based in primary and community care clinics). DMHP personnel in control districts are trained in telephonic counselling for mental health and suicide which they apply while carrying out follow-up calls for suicide attempts. Moreover, the DMHP in the control districts carry out monthly mental health awareness raising camps in the community to increase awareness around mental health and their services (this is not occurring in the intervention districts). The CASP team will also provide a brief training with DMHP staff in control districts covering suicide, its prevalence and associated risk factors, and myth busting around suicide prevention.

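### The re-attempt comparison between arms is fixed as a binomial test, with no covariate or district term, in a non-randomised design of two districts against two

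*Protocol article*

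**What the plan says.** The Study design section describes a "1:1 non-randomized, controlled pilot study" with Balod and Rajnandgaon as intervention districts and Mungeli and Balodabazar as control districts. The Aims section lists among the secondary aims the "Difference in rate of suicide re-attempt at 6 and 12 month follow up between intervention and control groups". For that comparison, Data analysis (Clinical outcomes, item 1) says that "we will use Bayesian binominal testing as implemented in the open software program JASP". It names no covariate and no term for district.

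Item 2 of the same section treats the score outcomes differently. Change in depression and suicidal behaviour "within the intervention group will be calculated using Bayesian linear mixed models as implemented in JASP", and for these models the protocol adds: "Models will be estimated both with and without a random effect for location". Baseline adjustment appears only in item 4, for the seemingly unrelated regression models of the cost-utility analysis, which rest on a sub-sample of 100.

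The Setting section gives the make-up of the districts. For Rajnandgaon it is "26% Scheduled Tribe (ST) and 10% Scheduled Caste (SC) communities". For Balodabazar it is "23.37% Scheduled Castes (SC) and 12.8% Scheduled Tribes (ST").

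**The concern.** The question concerns two observed proportions, whereas a binomial test sets one observed proportion against a fixed value. If the control percentage were entered as that value, its sampling error would drop out of the analysis.

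Even if a two-group test is meant, the named method has no place for the two features that matter most here. Arm follows district and was not randomised, so differences between the districts' patients go into the estimate. People in one district may also share a level of risk, so an analysis that treats them as independent gives intervals that are too narrow. The protocol considers location where the arms are not compared and leaves it out where they are.

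Re-attempt is the only clinical outcome compared between the arms. It is therefore the figure most likely to be cited as controlled evidence that CASP works.

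**Working it through.** **Inputs from the protocol.** Sample size section: 250 per arm, 20% loss, 10% control rate at 12 months, 10-point reduction, 80% power, two-sided 5%. Setting section: district populations (millions) and Scheduled Tribe (ST) and Scheduled Caste (SC) shares. **Assumptions.** An even split between districts, and the ICC, which the protocol does not give.

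**1. The planned size contains no allowance for clustering.** The pooled two-proportion formula is n = [1.96·√(2p̄(1−p̄)) + 0.8416·√(p₁(1−p₁)+p₂(1−p₂))]² / (p₁−p₂)².
- 20% v 10%: (0.990 + 0.421)² / 0.01 = 199 per arm, and 199/0.8 = 249. This matches the stated 250.
- 10% v 0%, the literal inputs: 74 per arm, and 74/0.8 = 93. This does not match.

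Which rates were meant is a separate matter. The calculation that matches 250 is an individual-level, two-sample one with a design effect of 1.

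**2. Literal one-sample reading.** Evaluable per arm: 250 × 0.8 = 200. At a rate of 10%:
- SE with the control rate treated as known: √(0.1×0.9/200) = 0.0212
- SE of a difference: √(2×0.1×0.9/200) = 0.0300
- Ratio: √2 = 1.41
- True error of a nominal 5% test: 2·[1−Φ(1.96/1.41)] = 16.6% (simulation 16.8%)

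**3. Two-proportion reading, district ignored.** With 100 evaluable per district, the design effect is DE = 1 + 99·ICC, the SE is understated by √DE, and the true error is 2·[1−Φ(1.96/√DE)].

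| Assumed ICC | DE | √DE | True error of a nominal 5% test |
|---|---|---|---|
| 0.001 | 1.10 | 1.05 | 6.2% |
| 0.005 | 1.50 | 1.22 | 10.9% |
| 0.01 | 1.99 | 1.41 | 16.5% |
| 0.02 | 2.98 | 1.73 | 25.6% |
| 0.05 | 5.95 | 2.44 | 42.2% |

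A beta-binomial simulation with four districts, a 10% rate and no effect gave 10.5%, 16.2% and 25.3% at ICCs of 0.005, 0.01 and 0.02. With the literal one-sample test and an ICC of 0.01, the simulated error is about 33%.

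**4. Difference between the districts (population-weighted).**
- ST, intervention: (1.8×26 + 0.8×31)/2.6 = 27.5%
- ST, control: (1.31×12.8 + 0.70×10.37)/2.01 = 12.0%
- SC, intervention: (1.8×10 + 0.8×8)/2.6 = 9.4%
- SC, control: (1.31×23.37 + 0.70×27.76)/2.01 = 24.9%

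**5. What a model can carry.** At a 10% rate, 400 evaluable participants give about 40 events, which supports only a few covariates. Two districts per arm leave 2 degrees of freedom between districts (critical t of 4.30 instead of 1.96), so the data cannot estimate the between-district variance well.

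**The case against.** - **The label may be loose.** The surrounding sentences speak of a difference between intervention and control, and nothing says that the control rate is a fixed test value. This stands. A reader might infer that the plan certainly runs a one-sample test, but the text supports that only as the literal reading. The missing covariates and district term do not depend on it.
- **The error rates are frequentist and the plan is Bayesian.** This stands too: the percentages show how far uncertainty is understated and are not properties of the planned Bayes factor. With a Bayes factor cut-off of 3 and uniform priors (neither is in the protocol), simulation under no effect gives about 4.7% false positives for the literal one-sample test and 0.6% for a two-sample test.
- **The size of any confounding is unknown.** The ST and SC shares describe general populations, not people who present after an attempt, and the protocol gives no risk by group. A reader might want to put a figure on the bias; the documents do not support one.
- **The services in the control districts are not a baseline imbalance.** The protocol notes monthly camps there to raise "awareness around mental health and their services (this is not occurring in the intervention districts"). It would be tempting to count these and the DMHP staffing as confounders. DMHP care is the comparator by definition, the camps are described as part of the same condition, and patient covariates would not remove either.
- **A statistical analysis plan may add adjustment.** Covariate lists and priors can indeed wait for it. But the article fixes a named method that cannot carry them, while it does specify location for item 2 and baseline adjustment for the cost analysis.
- **This is a pilot.** Re-attempt is secondary, is called preliminary, and is absent from the progression criteria. This stands and lowers the severity.

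**Conclusion.** The point holds for the re-attempt comparison. As written, the analysis gives an unadjusted contrast between non-randomised districts, with uncertainty understated for any positive variation between districts. The understatement of the SE is a factor of 1.05 to 2.44 for ICCs of 0.001 to 0.05; this range is assumed and rests on about 100 evaluable participants per district. A further factor of 1.41 applies only if the test is run literally as one-sample.

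Two stronger conclusions do not follow. Re-attempt is not the only comparison between arms, since the cost-utility analysis is also one and is baseline-adjusted; it is the only clinical one. Nor would a better model yield a causal estimate: with arm nested in two districts against two, no analysis can separate the effect of CASP from that of district. The severity is should-fix.

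**What to change.** Replace the binomial test in item 1 with a two-group Bayesian logistic regression of re-attempt, including suicide death, on arm at 6 and at 12 months.

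- Adjust for a short prespecified set of baseline covariates available in both arms: age, gender and method of attempt from the nurses' record books, and caste/tribe if the demographic survey is completed in control districts. Prior attempt is not readily available, because the baseline C-SSRS is listed only for the intervention group.
- Report the adjusted risk difference with a 95% credible interval, and the unadjusted two-sample comparison alongside.
- Show results by district. As a sensitivity analysis, add a district intercept under a stated range of priors on its standard deviation, because the result will depend on that prior.
- State that arm and district effects cannot be separated, and word the finding as a preliminary association.

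The cost is a rewritten analysis paragraph, a wider interval and a short demographic form for control participants. The data collectors who already take written consent in the control districts could complete it. Recruitment and follow-up are under way, so the form may be incomplete for those already enrolled. The Discussion reports a lack of systematic recording in the control districts, so the completeness of the record books there should be checked before the covariates are fixed.
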